## Abstract

**Background:**

The NOURISHED study: Nice OUtcomes for Referrals with Impulsivity, Self Harm and Eating Disorders.

Eating Disorders (ED) and Borderline Personality Disorder (BPD) are both difficult to treat and the combination presents particular challenges. Both are associated with vulnerability to loss of mentalization (awareness of one’s own and others’ emotional state). In BPD, Mentalization Based therapy (MBT) has been found effective in reducing symptoms. In this trial we investigate the effectiveness and cost-effectiveness of MBT adapted for Eating disorders (Mentalization Based Therapy for Eating Disorders (MBT-ED)) compared to a standard comparison treatment, Specialist Supportive Clinical Management (SSCM-ED) in patients with a combination of an Eating Disorder and either a diagnosis of BPD or a history of self-harm and impulsivity in the previous 12 months.

**Methods/Design:**

We will complete a multi-site single-blind randomized controlled trial (RCT) of MBT-ED vs SSCM-ED. Participants will be recruited from three Eating Disorder Services and two Borderline Personality Disorder Services in London. Participants allocated to MBT-ED will receive one year of weekly group and individual therapy and participants allocated to SSCM-ED will receive 20 sessions of individual therapy over 1 year. In addition, participants in both groups will have access to up to 5 hours of dietetic advice. The primary outcome measure is the global score on the Eating Disorders Examination. Secondary outcome measures include total score on the Zanarini BPD scale, the Object Relations Inventory, the Depression Anxiety Stress Scales, quality of life and cost-effectiveness. Measures are taken at recruitment and at 6 month intervals up to 18 months.

**Discussion:**

This is the first Randomised Controlled Trial of MBT-ED in patients with eating disorders and symptoms of BPD and will provide evidence to inform therapy decisions in this group of patients. During MBT-ED mentalization is encouraged, while in SSCM-ED it is not overtly addressed. This study will help elucidate mechanisms of change in the two therapies and analysis of therapy and interview transcripts will provide qualitative information about the conduct of therapy and changes in mentalization and object relations.

**Trial registration:**

ISRCTN51304415

## Background

Patients with eating disorders (ED) combined with symptoms of borderline personality disorder (BPD) present particular therapeutic challenges. Symptoms include weight loss, bulimia, self harm, emotional lability and impulsive behaviours. During treatment, while some symptoms may improve, others can worsen. Therefore treatment needs to address both the eating and personality disorders, and individuals with both conditions are more likely than those with eating disorders alone to have a complicated course with atypical disorders and migration from one disorder to another [1]. Borderline Personality Disorder has been shown to respond to Mentalization Based Therapy (MBT) [2] which targets vulnerability to loss of self-reflectiveness (mentalizing) which is thought to occur in both BPD [3,4] and Eating Disorders [5,6]. This project will test whether MBT is an effective treatment for this troubled group of patients.

Eating disorders are among the most common causes of ill health in young people, affecting some 3-4% of women and 0.3% of men [7,8]. The morbidity associated with eating disorders is of several types. Low weight, electrolyte imbalance and nutrient deficiency leads to serious physical problems which can be fatal if extreme. Other problems include depression and anxiety [9], social isolation, family, relationship and occupational difficulties and a substantially reduced quality of life [10]. BPD has a prevalence of 0.7% but a roughly equal sex distribution [11,12]. It has a broad impact on psychological, family and social functioning [13]. Symptoms include mood fluctuations, including depression, outbursts of anger, deliberate self harm, suicidal behaviour and disturbed relationships.

The two sets of conditions occur together more commonly than would be expected. The combination of Eating and Borderline Personality Disorder symptoms was noted by Lacey [14] who found that 80% of a series of patients with bulimia nervosa engaged in at least three self damaging behaviours and coined the term “Multi-impulsive bulimia”. The proposed trial will study this group, although the criteria and the name given, (ED with symptoms of BPD), differ. Lacey [14] and Zeeck et al [15] pointed out their very severe morbidity and the difficulties in treatment they present. The direct and indirect costs of these problems have not been reported, although the costs of ED [16-18] and BPD [19] are both high. Moreover, there is some evidence [14,20] that engagement in treatment of patients suffering from both disorders is poor.

It has been shown that nearly 30% of ED patients meet criteria for any personality disorder, while 6.2% have BPD [21]. In the present study, patients with ED complicated by some of the most damaging BPD symptoms, namely suicidal behaviour, deliberate self harm and impulsive behaviours (although not always fulfilling all BPD criteria) will be included. A review of recent patients treated at the Eating Disorders Unit at the main study site, St Ann’s Hospital, suggested that some 20% of patients seen fulfilled study criteria. Treatment of eating disorders has a limited evidence base: Cognitive Behaviour Therapy (CBT) for bulimia nervosa and binge eating disorder is the only treatment for which NICE has cited class A Randomised Controlled Trial (RCT) evidence [18]. For Borderline Personality Disorder, Mentalization Based Therapy [22], Dialectical Behaviour Therapy (DBT) [23] and Cognitive Behaviour Therapy [24] have shown benefit in RCTs. NICE [25] calls for more Randomised Trials to evaluate all these and other therapies. For patients with both ED and BPD, DBT has shown promise in small pilot studies [26,27]. MBT has a theoretical basis in attachment theory and deficits in primary attachments have been shown in both Eating Disorders [28] and Borderline Personality Disorder [29]. Skårderud [30,31] has argued for the importance of impaired mentalization and the relevance of MBT in in anorexia nervosa. MBT therefore has a theoretical basis which may have significance for the aetiology as well as the treatment of ED/BPD. We have therefore used MBT in the current trial, adapted for participants with Eating Disorders and the modified therapy is called MBT-ED [32].

Specialist Supportive Clinical Management (SSCM) was developed as a control therapy in trials of treatment for anorexia nervosa [33]. We chose it as a control treatment because it is a manualized treatment that approximates to treatment as usual for eating disorders. In the current trial patients can have any eating disorder diagnosis, and so the Therapy manual for SSCM was adapted for use with any eating disorder and the modified therapy called SSCM-ED. Except for the paragraph headed “Control condition” below, we have used the terms MBT and SSCM in this paper to indicate the modified therapies used in the study.

The intended participants in this trial suffer from complex problems which can adversely influence clinical care. We therefore embarked on a randomized controlled trial of Mentalization Based Therapy against Specialist Supportive Clinical Management in patients with a diagnosis of an eating disorder and either BPD or symptoms of BPD and here present the protocol for that study.

### Objectives of the trial

#### Primary objective

To ascertain whether Mentalization Based Therapy is clinically effective at reducing observer rated symptoms of Eating Disorder, using an accepted measure, the Eating Disorders Examination, in patients with combined eating and borderline personality disorder symptoms up to 18 months post randomisation compared to Specialist Supportive Clinical Management.

## Methods

### Study design

This is a multi-centre study across five Clinical Centres, three NHS Eating Disorder Units and two NHS Personality Disorder Units in three different NHS Trusts.

The design is a single-blind (researchers being blind) randomised controlled trial of Mentalization Based Therapy for eating disorders (MBT-ED), with an intensity of one individual and one group session per week for one year, compared to Specialist Supportive Clinical Management adapted for all eating disorders (SSCM-ED), a standard treatment for eating disorders, which comprises one session every 1 to 4 weeks for 20 to 26 sessions All trial participants have access to 5 hours of dietetic advice over the course of treatment.

Participants will be recruited from the participating clinics and will include both new referrals and patients currently receiving care. Randomisation will be remote so ensure researcher blindness to treatment allocation.

Treatment will begin following randomization for 12 months (MBT-ED group) or for up to 12 months (SSCM-ED group). All participants will be asked to complete assessment questionnaires and to participate in assessment interviews at 6, 12 and 18 months follow-up.

### Participants

Inclusion criteria

1. Over 18

2. Eating Disorder diagnosis (DSM IV [35])

3. BPD symptoms

4. Able and willing to provide written informed consent

The criteria for “BPD symptoms” are that the patient fulfils both behavioural criteria of the DSM IV, namely 1. impulsivity in at least two areas that are potentially self-damaging (e.g. spending, sexual behaviour, substance abuse, reckless driving, binge eating). 2. recurrent suicidal behaviour, or self-mutilating behaviour.

Exclusion criteria

1. Current psychosis based on the MINI examination [36]

2. Current inpatient or day-patient (attending 3 or more days per week)

3. Currently in individual or group psychological therapy

4. Received MBT <6 months prior to randomization

5. Organic brain disease leading to significant cognitive impairment

6. Body Mass Index (BMI) less than 15 kg/m^2^ (Normal range 19-25, Anorexia Nervosa <17.5)

### Design and procedure

#### Recruitment and consent

We aim to include all patients with current eating disorders and Borderline Personality Disorder symptoms as defined above. Participants may be underweight, normal weight or overweight, although because of the increased risk of physical decompensation those severely malnourished (with a BMI of under 15) are excluded. We will therefore be assessing the effectiveness of MBT in patients with different eating and weight problems. In addition to their eating disorder, we anticipate that most participants will have current self harm and impulsive behaviours and a sub-group will fulfill all criteria for BPD. In addition, a group of participants will fulfill criteria for BPD without necessarily experiencing self harm or impulsivity.

The initial introduction to the study will come from the treating clinician. If interested in obtaining more information, the clinician will provide the Participant Information Sheets and Carer Information Sheets. At least 24 hours later, the potential participant will be approached by a member of the research team and if still interested, an interview time arranged. At that meeting the study will be described, outstanding questions answered and the potential participant asked to sign the consent form which will be countersigned by the member of the research team.

The participant will then receive the following interviews:

Eating Disorders Examination (EDE) [37,38]

Reflective Function Questionnaire (RFQ)^a^

Reading the mind in the eyes test [39].

Object Relations Inventory (ORI) [40].

Acts of Deliberate Self Harm Inventory (ADSHI) [41].

MINI International Neuropsychiatric Schedule (MINI), [36].

Structured Clinical Interview for DSM-IV Axis II Personality Disorders (SCID-II), [42].

Global Assessment of Functioning (GAF) [35].

Zanarini-BPD (ZAN-BPD) [34].

Euroqol (EQ5D) [43].

Depression, Anxiety, Stress Scales -21 (DASS 21) [44].

Modified Social Adjustment Scale (SAS) [45].

Adult Service Use Schedule (AD-SUS) [46].

Big Five personality Inventory (BFI) [47].

Apart from the MINI and the SCID II which are only administered at baseline for diagnostic purposes, all instruments will be repeated at 6, 12 and 18 months post randomization.

The original signed consent form will be retained in the Investigator Site File, with a copy in the participants’ hospital medical notes, and a copy retained by the participant for their information. The participant will specifically consent to their General Practitioner (GP) being informed of their participation in the study.

The right to refuse to participate without giving reasons will be respected.

#### Trial monitoring safety assurance

Three trial monitoring committees will be formed:

1. Trial Management Committee (TSC): This will manage the day to day running of the trial and comprise the Chief Investigator, the Trial Manager and relevant members of the research team, as appropriate. It will meet weekly.

2. Independent Data Monitoring Committee (iDMC): This will have an open and a closed session at each meeting. The chair will be an independent academic and members will include an independent Eating Disorders expert and an Independent general Academic Psychiatry expert. The Chief Investigator and the Trial Statistician, who will provide reports, the Trial Manager and the Trial Statistician will be in attendance. Of the latter, only the Trial Statistician will attend the closed part of the meeting. In the closed part, summaries of follow-up assessments and adverse events, will be available for each of the treatment groups (labelled a and b). iDMC meetings will be held annually, or more often if required and the chair will advise the Trial Steering Committee of their recommendations regarding continuation, stopping early or modifications to the protocol.

3. Trial Steering Committee (TSC): The TSC will be chaired by an independent expert and members will include experts in Eating Disorders and General Psychiatry (different from those in the iDMC) as well as user and carer representatives, a lead trust representative and the Chief Investigator, who will provide a report, the Trial Manager and the Trial Statistician. Meetings will be annual, or more frequently should the need arise.

#### Randomisation, allocation concealment and protection against bias

Due to the nature of the intervention blinding of participants and therapists will not be possible. However the Trial Statistician and Research Workers responsible for the collection of the assessments will remain blind to treatment allocation during the trial and primary analyses. Participants will be asked to be careful not to divulge what sort of therapy they have had, or other information that could interfere with the Research Worker’s blindness to treatment group.

Following completion of the baseline questionnaire, patients who consent to take part in the trial are randomly allocated to MBT or SSCM (ratio 1:1) by sites via an online system based at the King’s Clinical Trials Unit based at the Institute of Psychiatry in London. The method of randomisation of participants will be by block randomisation stratified by BMI (15.0-18.5, 18.6-24.9, >25) and service type (eating disorders unit or personality disorders unit). Randomly varying block sizes will be implemented in order to maintain pre-randomisation allocation concealment.

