### Statistical analysis

#### Power calculation

An overall sample size of 140 (randomised 1:1) would provide over 90% power to detect an effect size of d=1.07 on the Global EDE Score using an analysis of covariance with 2 sided 5% significance tests. This calculation is based on the conservative assumption of a zero correlation between baseline and post treatment scores on the EDE and allows for clustering within therapy groups and 25% attrition. The effect size (1.07) was based on a minimal clinically important difference, at 18 months post randomization, of 1.5 on the EDE, with a pooled standard deviation of 1.4 [38]. The MBT arm consists of a group treatment so has been inflated to allow for correlation between the measures of those participants in the same group therapy Assuming an average group size of 10 and an intraclass correlation between Global EDE scores of 0.07 we considered a design effect of 1.63.

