#### Analysis

Statistical analysis will be carried out in Stata. Mediation modeling may require the use of specialist structural equation modeling software (e.g. Mplus). All treatment group comparisons will be carried out on an intention-to-treat basis, that is subjects will be analysed in the group to which they were randomised irrespectively of the treatment received.

The primary and secondary longitudinal outcomes will be analyzed using linear mixed modelling (LLM) [51]. In this model the outcome variable measured at the post treatment time points (here 6, 12 and 18 months) is the dependent variable with outcome at baseline (EDE), treatment (MBT or SSCM), time (12 or 18 months), a treatment × time interaction and stratification factors (BMI and service type) as covariates. To account for correlation between repeated measures on the same individual a subject varying intercept will be included. To allow for correlation between EDE measures within the same therapy group, a further random effect will be included that varies with therapy arm.

Treatment effects on any secondary outcomes will be assessed in the same way, allowing for any deviations from a non-normal data by generalisations of the LMM.

Analyses that are based on maximum likelihood and will provide valid inferences under a missing at random (MAR) missingness mechanism. Sensitivity analyses will be used to assess the robustness of conclusions to missing outcome data and to departures from randomised treatment in the manner of [52].

Analyses of mediation at 18 months will use a regression approach as described by Holmbeck [53], [54], together with more recent statistical methods [54] to allow for possible hidden confounding between the mediator and outcome.

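### The Trial Statistician is at most masked by arm label during the trial, and that mask cannot survive fitting the primary model, although the protocol claims blinding through the primary analyses

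*Protocol article*

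**What the plan says.** Under Randomisation, allocation concealment and protection against bias, the protocol article says that the "Trial Statistician and Research Workers responsible for the collection of the assessments will remain blind to treatment allocation during the trial and primary analyses". The sentence covers two roles and two periods and carries no qualification.

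Under Trial monitoring safety assurance, the entry on the data monitoring committee (iDMC) lists "The Chief Investigator and the Trial Statistician, who will provide reports" among those present. Of the trial staff attending, "only the Trial Statistician will attend the closed part of the meeting". In that part, "summaries of follow-up assessments and adverse events, will be available for each of the treatment groups (labelled a and b"). Meetings are at least annual.

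Under Analysis, the primary model is a linear mixed model. It includes this term: "To allow for correlation between EDE measures within the same therapy group, a further random effect will be included", one that the same sentence says varies by arm. Under Power calculation the protocol explains where such clustering arises: "The MBT arm consists of a group treatment". The abstract and the intervention sections describe SSCM as individual sessions, with no group component.

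**The concern.** The blinding statement is offered as a protection against bias, and a later report could repeat it. Two other parts of the protocol limit what it can mean for the Trial Statistician.

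First, someone who sees outcome summaries by arm while the trial is running knows the direction and size of the emerging difference, even when the arms are called a and b. Any analytic choice made after that point is open to the question of whether the interim results shaped it.

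Second, a model term that applies to only one arm identifies that arm to whoever codes and fits it. If so, the protocol promises a property for the primary analysis that its own model removes. A report that the primary analysis was done blind, resting on this statement, would be inaccurate.

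**Working it through.** The protocol gives no figure for this point, so the check is a comparison of its sections, taken one period at a time.

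**During the trial**

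1. The promise is blindness to allocation (Randomisation section).
2. The Trial Statistician provides reports to the iDMC and attends its closed part (Trial monitoring section).
3. The closed data are by-arm summaries under codes a and b. The EDE, which is the primary outcome, is among the instruments repeated at 6, 12 and 18 months (Recruitment and consent). Follow-up summaries can therefore reasonably be expected to include it, although the protocol does not list their content.
4. Coded summaries do not in themselves tell the reader which arm is MBT. They do show the difference between a and b.
5. Result: the statistician may remain unaware of arm identity but not of the accumulating comparison. That is label masking.

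**At the primary analysis**

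1. The model needs a term for shared therapy-group membership, described as "a further random effect will be included that varies with therapy arm".
2. MBT has weekly group sessions with at most 10 participants per group (Experimental condition). The sample size assumes an average group size of 10 and an intraclass correlation of 0.07, giving a design effect of 1 + (10 − 1) × 0.07 = 1.63, which reproduces the stated figure. The protocol ties this inflation to the MBT arm.
3. With 140 randomised 1:1, the MBT arm has 140 / 2 = 70 participants. At 10 per group that is about 70 / 10 = 7 groups. SSCM has none.
4. The dataset for the primary model therefore carries shared group identifiers for about 70 participants, all under one code. If SSCM participants are entered as clusters of one, or if the variance term is switched on for one arm only, the pattern is just as visible.
5. Result: whoever fits the specified model can see which coded arm is MBT.

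**A second route to the same end**

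The Analysis section also plans sensitivity analyses for departures from randomised treatment. Compliance is defined separately by arm: at least half of the individual and half of the group sessions for MBT, and at least half of the sessions offered for SSCM. The session schedules differ as well: weekly individual plus weekly group therapy for a year, against 20 sessions with up to 6 more. Attendance data would reveal the arms without the group identifier.

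**How much choice remains open**

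The Analysis section fixes most of the model, but not all of it. It takes the outcome at 6, 12 and 18 months as the dependent variable, yet defines the time covariate with only the 12- and 18-month levels. Whether the 6-month data enter the model is therefore still to be settled, and by someone who may by then have seen by-arm results.

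**The case against.** The strongest reply is that the two sections do not conflict during follow-up. The promise concerns allocation, and coded summaries are a way to report by arm without disclosing it. Nothing says that group identifiers, attendance or session counts enter the closed reports. This stands: showing a and b data does not by itself contradict blindness to allocation.

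A reader might also infer that the statistician's place on the Trial Steering Committee (TSC), listed as "the Chief Investigator, who will provide a report, the Trial Manager and the Trial Statistician", breaks the blind or calls for exclusion from its decisions. The document does not support that. It does not say that the TSC sees by-arm data, and it makes the iDMC chair the channel for recommendations. Membership reveals no allocation.

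It can further be said that an analysis plan or an iDMC charter, neither shown, may settle who holds the code and when identifiers are released. That is fair, and the absence of such detail is not the complaint. The complaint is that the article makes an unqualified claim through the primary analyses and specifies a model that is incompatible with it if the same person fits it.

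Finally, the design is defined as single-blind with the researchers blind. Assessor blinding is the main protection for the interview-rated EDE, and it is untouched. That stands too, and it limits the importance of the point.

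**Conclusion.** The point holds in a limited form. During the trial the Trial Statistician is masked by label at most and knows the emerging between-arm difference once closed reports contain follow-up data. At the primary analysis even the label mask fails, because the therapy-group term identifies the MBT arm.

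It would be tempting to conclude that the stated blinding does not exist. The documents do not support this: Research Worker blinding is unaffected, and the a and b code can hold throughout follow-up if group and attendance data are withheld from the statistician.

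No bias in the treatment effect can be quantified from the document. What can be stated is the exposure: by-arm summaries at least yearly once follow-up data are reported, and group identifiers for about 70 of 140 participants at the analysis. The conclusion assumes that the Trial Statistician fits the primary model, since the article names no other statistician, and that the closed summaries include the EDE. This is an inaccurate statement about protection against bias that should be corrected; it does not invalidate the trial.

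**What to change.** 1. In the randomisation section, keep the full blinding claim for the Research Workers only.
2. State there that the Trial Statistician sees coded by-arm summaries from the first closed iDMC report, and is masked by label only, until therapy-group or attendance data are released for the primary model.
3. Sign off the primary model, the 18-month contrast and the sensitivity analyses before the first closed report that contains follow-up data. The sign-off should settle which time points enter the model. If a dated analysis plan already does this, a reference to it is enough.

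The cost is protocol wording and possibly an earlier sign-off date. The downside is a less favourable blinding claim and less freedom to revise the analysis later. The sample size and the committee membership do not change.
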